#### Process Evaluation Data Collection

Data are collected to assess the quality of program implementation. Research assistants are present at each intervention session and complete a fidelity form to ensure consistent implementation of the intervention or control program as intended as well as unforeseen barriers to implementation. These feedback forms are reviewed by the lead facilitators and PI regularly to provide immediate feedback to facilitators should mid-point corrections be needed.

Youth also complete a feedback form at the end of each session which is reviewed by the facilitators and research assistant to gauge youth interest and engagement in the topics and to make mid-point adjustments to program content and delivery as needed.

In addition to the end of program survey that encourages youth to provide feedback on the entire 18-hour curriculum, after completion of the T3 (final) follow up survey, youth in the intervention arm are invited to participate in a semi-structured interview about their experiences with the program. Interviews with site leads and facilitators provide additional feedback on the program to guide ongoing implementation including sustainability in the participating neighborhoods. Collectively, process evaluation data will be used to inform and improve the intervention content and implementation guidance.

### 6.3 MEASURES TO MINIMIZE BIAS: RANDOMIZATION AND BLINDING

#### Assignment of Interventions

##### Randomization

Randomization was performed at the neighborhood level (i.e., cluster) to reduce risk for contamination. The initial randomization included 10 clusters that were assigned to experimental or control conditions. The study statistician performed this randomization, stratifying by lead site in that neighborhood (YMCA, Urban League, or Other), such that within each stratum, each site/neighborhood had a 50/50 chance of being assigned to intervention or control. Due to a combination of lower-than-expected recruitment by neighborhood (target=96 participants each) and the interest from other community partners, we individually randomized an additional 11 neighborhoods, stratified by type of site. This resulted in a total of 21 clusters randomized, with 11 assigned to experimental and 10 assigned to control. All neighborhoods in the study met the original criteria of being socially or economically disadvantaged and/or predominantly African American.

##### Blinding

Randomization was performed after approval for the study was obtained for a site in a new neighborhood so that the randomization assignment would not influence a site's willingness to participate. Notably, the PI was blinded from randomization until she had successfully recruited a site to participate in the study. Due to the study design, investigators, research staff, community partners, facilitators, and youth participants could not be blinded to study assignment.

## 6.4 STUDY INTERVENTION/EXPERIMENTAL MANIPULATION ADHERENCE

### Retention in Program

Once community partners recruit youth, retention throughout the 18-hour curriculum is a key focus. Upon enrolling in either the control or experimental arm, prospective participants received program information, signed an assent form and completed a contact information sheet. Research assistants ensure that the document is legible and that all fields are completed. Research assistants use this information to contact the participant prior to each session to remind them of the session. If youth are not present at the beginning of a session, research assistants and facilitators will contact the participant to encourage them to join late. Retention is facilitated by collecting detailed contact information and offering incentives for survey completion (\$50 total for baseline, feedback surveys throughout the program, and EOP; \$30 for T2; \$50 for T3) (see Figure 1 for study flow).

## 6.5 CONCOMITANT THERAPY

N/A

### 6.5.1 RESCUE THERAPY

N/A

## 7 STUDY INTERVENTION/EXPERIMENTAL MANIPULATION DISCONTINUATION AND PARTICIPANT DISCONTINUATION/WITHDRAWAL

### 7.1 DISCONTINUATION OF STUDY INTERVENTION/EXPERIMENTAL MANIPULATION

A participant may stop participating and withdraw from the study at any time. If a subject discontinues from either arm but not from the study, remaining study procedures will be completed as indicated by the study protocol.

Additionally, a participant may be considered too disruptive for participation in the program (control or intervention) and be asked to discontinue their attendance in the program.

The data to be collected at the time of study intervention discontinuation may include the reason(s) for discontinuing from the intervention, and methods for determining the need to discontinue

### 7.2 PARTICIPANT DISCONTINUATION/WITHDRAWAL FROM THE STUDY

Participants are free to withdraw from participation in the study at any time upon request. An investigator may discontinue a participant from the study for the following reasons:

- Request from parent or adult caregiver to discontinue their participation
- Lost-to-follow up; unable to contact subject (see **Section 7.3, Lost to Follow-Up**)
- Any event or medical condition or situation occurs such that continued collection of follow-up study data would not be in the best interest of the participant
- The participant meets an exclusion criterion (either newly developed or not previously recognized) that precludes further study participation, i.e., moving out of Pittsburgh

The reason for participant discontinuation or withdrawal from the study will be recorded. Any subject that withdraws from the study, before any data collection is completed, such as survey responses, consent and assent forms will be kept and filed with withdrawn/declined records.

### 7.3 LOST TO FOLLOW-UP

A participant will be considered lost to follow-up if he fails to respond to at least 10 contact attempts for follow up surveys and the 3 months window for follow up survey completion has passed.

Missing sessions (not participating in the program) will not be considered a reason for loss to follow up. We will make every attempt to reach participants who are missing sessions including using all contact information provided as well as through the community facilitators in their neighborhood.

Before a participant is deemed lost to follow-up, the investigator or research team member will make every effort to regain contact with the participant. These contact attempts will be documented in the participant's study file. Should the participant continue to be unreachable, he will be considered to have withdrawn from the study with a primary reason of lost to follow-up.

## 8 STUDY ASSESSMENTS AND PROCEDURES.

### 8.1 ENDPOINT AND OTHER NON-SAFETY ASSESSMENTS

#### **Assent and Consent**

Adolescent males ages 13-19 receive a description about the research study and parental letter about the study from the community sites. The parent letter include an option for parents/caregiver to decline their child's participation. We received a waiver of parental permission and waiver of signed consent from the University of Pittsburgh Human Subjects Research Protection Office. Research assistants review the verbal consent form with youth at the beginning of the first session and answer any questions pertaining to confidentiality, the program flow, and survey time points. The consent form covers all 3 waves of data collection, Time 1 through Time 3 as described earlier.

#### **Data Collection**

There are several points of data collection throughout the study, starting at baseline all the way through T3: baseline surveys, feedback forms, End of Program (EOP) survey, T2 and T3 follow up surveys. The surveys are all anonymous, linked by a personal study code that youth create by answering a series of questions that only they know the answer to at the beginning of each survey. This method of using a personal study code was selected to ensure anonymity and increase the likelihood of honest responses.

In addition to survey data, other sources of data for this study (primarily for process evaluation and assessing intervention fidelity) include: 1) feedback forms completed by youth after the end of each session; 2) fidelity forms completed by research assistants at each session; 3) interviews with site leads and facilitators; 4) confidential interviews with youth (after Time 3 data collection).

### **Main Study Phase:**

**Baseline survey:** Youth are asked to complete the baseline survey the first time they attend a session (can enter study at Sessions 1 – 3; if participant is interested in joining, they are asked to return for the next round). All sites conduct web-based surveys (back up paper surveys are used as needed) on tablets using REDCap, an online data management and survey system. Responses to the anonymous web-based secure survey are entered by the youth participants themselves on an electronic tablet; no data are stored on the computers themselves. Only research staff who have been added to the project can access this online database. Data are downloaded and stored on a password-protected share drive that can only be accessed by users with the appropriate permissions. No names are connected to the survey data as each participant creates their own secret code as described above.

**End of program survey:** At the end of the program, youth are asked to complete an end of program survey that asks about which sessions they attended, their impressions of the program, as well as some additional school and community related questions (about connectedness to school, suspensions, social supports, important adults). Surveys are self-administered on electronic tablets provided by the research staff (back up paper surveys will be used if tablets are not available or fail). All participants, regardless of amount of curriculum completed, are eligible to take this survey; participants are asked to complete the end of program survey later if they miss the last session.

### **Follow up surveys (T2 and T3):**

Participation in the 3- and 9-month follow-up surveys (T2 and T3 surveys, respectively) are facilitated via tracking of participants with the help of community partners at each site. Youth provide detailed contact information at baseline to facilitate follow up. Contact information is confirmed again at sessions following the baseline survey, and at the T2 survey. Youth are also called or texted periodically by research assistants between follow-up surveys to ensure that contact information is still valid. Finally, for those that miss an EOP or T2 survey in the appropriate time frame, a comprehensive “make-up” survey is offered (with the same monetary compensation) to update contact information and increase the likelihood they’ll participate in the next survey.

Follow up surveys are administered approximately three months (T2) and nine months (T3) after the end of the program. Surveys are offered in English and are completed by youth on electronic tablets provided by the research staff (back up paper surveys will be used if tablets are not available or fail). T2 and T3 surveys are similar to the survey administered in Time 1 and aim to assess intervention effects on knowledge, attitudes, self-efficacy, and behaviors regarding addressing disrespectful behaviors toward women and girls among adolescent males. Community sites where the program was held will facilitate reconvening participating adolescents and have agreed to convene these groups of adolescents (regardless of whether they have continued involvement with that site). All participants, regardless of amount of curriculum completed, are eligible to take these surveys.

**Emailed/text survey option:** Participants who cannot attend the study site or other community site (e.g., due to lack of transportation, neighborhood barriers) for EOP or follow up survey administration will be offered the option to take the survey via email or a texted link on an internet-capable device (e.g., computer, smartphone). The RA will confirm via phone that the participant is OK to take the survey. The email address from our study team will say [contact] (or an RA work phone number if the link is texted to participant) and RA number to call or text with any questions or concerns. The link will be specific to the email address that the young person provides and will only allow the survey to be taken

once. Using REDCap's anonymous survey feature, we can create an individualized link, send to participant's email or phone, and see if their survey was completed, but we cannot determine which survey data corresponds to that participant (i.e., remains anonymous). Phone call option: participants can also opt to complete the survey during a phone call with a research assistant, who reads aloud the questions and the participant responds; the research assistant enters the answers directly into the online survey tool.

Alternate contact information: We will also use the alternate contact information provided by youth upon study enrollment to reach them for follow up surveys. This may include, but is not limited to, phone numbers or email addresses for parents, caregivers, other family members, and close friends. We then ask these contacts to facilitate us reaching the participant. Community site partners from the program are also contacted to ask for retention assistance.

Interviews: At or after Time 3, some youth will be invited to participate in a confidential interview about their experiences receiving the control or intervention, their feedback about the relevance of the program, and additional input about the impact of the program on themselves and their peers. The interviews will be digitally recorded, transcribed, and the audiofiles destroyed once the transcription has been checked for accuracy and all identifying information removed.

Follow up procedure for youth who are in placement/incarcerated: Research staff may contact the youth's parents/caregivers through the contact information the youth have provided to arrange administration of follow up surveys per protocol. When the research staff learns from the parent/caregiver, another individual or agency on the contact information sheet, or from the site lead where the program was originally held that a participant is in placement (i.e., at a detention center or locked facility), the research team will offer several options for conducting the follow up survey. 1) The adult caregiver/parent who has contact with the participant can provide information to the participant about how to complete the follow up survey (the research team will provide their contact information); 2) [name] can send a message to the placement site to convey a message to the participant ([Name of participant] is due to complete a survey as part of a young men's study. This is completely voluntary. Please provide this message to the participant. For example, "[name] is trying to reach you to ask you to complete the follow up survey from the young men's program. You can reach her at [contact] or by emailing her at [[contact]](mailto:[contact])"); 3) If the detention center/placement facility is willing, and the participant is interested in completing the survey while incarcerated, the research team will come to the facility to meet the participant at a time designated by staff. The survey will be administered on a password protected, wireless computer notepad managed by the research team in a private area designated by staff at the facility; 4) the participant is interested in completing the survey while incarcerated, and the staff at the site are willing to assist, the staff will receive a link to the survey and the young person will complete the survey online on a designated computer. Staff will clear the browsing history on the computer. The youth will receive their incentive after they have been released from placement.

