## 6 STUDY INTERVENTION(S) OR EXPERIMENTAL MANIPULATION(S)

### 6.1 STUDY INTERVENTION(S) OR EXPERIMENTAL MANIPULATION(S) ADMINISTRATION.

#### 6.1.1 STUDY INTERVENTION OR EXPERIMENTAL MANIPULATION DESCRIPTION

##### **Experimental and Control Arms:**

Program Delivery: Both experimental and control arm interventions involve 18 hours of curriculum, generally spread out over 3 to 6 week periods. The program is delivered with some variation in schedules to meet the needs of community partners and participating youth. Such configurations include but are not limited to: three 6-hour sessions spanning three weekdays during the summer (for job skills training only), nine 2-hour sessions held twice per week on weekday evenings, and six 3-hour sessions held once or twice per week on weekday evenings or Saturday afternoons (which was the preferred and most commonly used design).

Fidelity to intervention: For both intervention and control arms, research assistants are present at every session to track attendance, facilitate program implementation logistics (such as ordering food), and to complete detailed fidelity forms that assess facilitators' ability to deliver the content of the program as intended.

**Manhood 2.0 (experimental arm):** Manhood 2.0 guides youth to explore and reflect upon social constructions of masculinity, describe healthy relationships, discuss healthy sexual behaviors, identify coercive and disrespectful behaviors, and practice skills to intervene when witnessing peers' disrespectful and harmful behaviors, with repeated reflection on gender norms throughout these sessions. The curriculum involved three main topic areas. The first focuses on the theme of gender, masculinity and power, allowing the young men to actively reflect on the messages and expectations that they have received from society about manhood and gender norms. The second topic focuses on the theme of violence. This includes several components: an exploration of the various forms of violence, its impact on communities, and the role that masculinity may contribute; identifying healthy versus unhealthy romantic relationships; sexual consent and decision making; and bystander interventions when witnessing abusive behavior. The final topic area focuses on sexual and reproductive health, which includes providing

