## Outcomes

All outcomes are collected via self-report on anonymous surveys by participants.

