### Primary Outcome:

**SV/ARA perpetration:** At baseline and T3 (9 months post-intervention), participants report whether they perpetrated the following SV or ARA behaviors in the last 9 months. The primary outcome measure for the study is any report of SV or ARA perpetration, i.e., yes to any of the following items.

The following two constructs focus on ARA behaviors against a dating partner. "Any ARA perpetration" is measured as a yes to any of these 13 items.

**Physical/Sexual relationship violence:** Three items are used to assess physical or sexual violence perpetration against a partner or ex-partner.(33) Participants report whether they performed each action, which is dichotomized as yes to any. Examples include "hit, pushed, slapped, choked or otherwise physically hurt someone you were going out with or hooking up with?" and "used physical force or threats to make someone you were going out with or hooking up with have sex (vaginal, oral, or anal sex) when they didn't want to?"

**Dating abuse:** A ten-item scale, developed for use with high school-aged students, is used to assess whether the participant perpetrated any abuse against a dating partner (34). Examples include "convinced them to have sex, after they said no a few times" and "told them not to talk to others or told them who they could hang out with." A positive response to any of these items is counted as any ARA perpetration.

"Any SV perpetration" is measured as yes to any of the sexual relationship violence and dating abuse items above as well as yes to any of the behaviors below.

**Non-partner sexual violence:** To measure whether a participant committed sexual violence against a *non-partner*, the two sexual IPV items were modified to query for people they had NOT gone out with or hooked up with, and included friends, family, and strangers (33). Responses are dichotomized as yes to any.

**Incapacitated sex:** Participants are asked if they had done something sexual with someone when that person was "too drunk or high to stop you,"(35) with a response of "yes" coded as yes to incapacitated sex.

**Use of drugs or alcohol on purpose for sex:** Participants are asked whether they had purposely given someone alcohol or drugs to do something sexual with that person(36). A response of "yes" is coded as yes to use of drugs or alcohol on purpose for sex.

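### The phone option lets an unblinded research assistant hear and enter T3 perpetration answers, contradicting the protocol's statements that outcomes are anonymous and self-entered

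*Protocol*

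**What the plan says.** Section 8.1, Follow up surveys (T2 and T3), offers completion on a tablet, by an emailed or texted link, or by phone. On the phone, "participants can also opt to complete the survey during a phone call with a research assistant, who reads aloud the questions" and "the research assistant enters the answers directly into the online survey tool".

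Other parts of the protocol describe something different:
- Section 8.1, Outcomes: "All outcomes are collected via self-report on anonymous surveys by participants".
- Section 8.1, Data Collection: every survey is anonymous, "linked by a personal study code that youth create by answering a series of questions that only they know the answer to". The reason follows: "This method of using a personal study code was selected to ensure anonymity and increase the likelihood of honest responses".
- Section 8.1, Data Management, and Section 10.1.9.1: the youth enter the survey data themselves.
- Section 4.1: baseline is completed in person on a tablet, and later surveys on a tablet or through a link. The phone is not listed.

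On the outcome, Section 8.1 states that "The primary outcome measure for the study is any report of SV or ARA perpetration", scored yes if any item is endorsed. On masking, Section 6.3 says "investigators, research staff, community partners, facilitators, and youth participants could not be blinded to study assignment". On contact with participants, Section 6.1.1 says "research assistants are present at every session to track attendance" in both arms.

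**The concern.** The primary outcome is a young man's own admission of sexual violence or relationship abuse, and one concealed yes can change his classification. The protocol's stated protection against concealment is anonymity. In the phone mode he speaks his answers to a staff member who knows whom she has called, who is not masked to arm, and who may have sat in on his sessions.

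Two things are at stake. First, the protocol describes the collection of its primary outcome inaccurately in several places. Second, a mode that weakens disclosure is available at the primary time point. If it suppresses reports equally in both arms, a true effect shrinks. If it suppresses them unequally, the estimated effect is biased. Because baseline is self-entered on a tablet, a phone survey at T3 also changes the mode between the baseline value used as a covariate and the outcome.

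**Working it through.** **1. The passages side by side.** The follow-up text has the assistant entering phone answers; Data Management and Section 10.1.9.1 have the participant entering them. The Outcomes and Data Collection text calls all surveys anonymous. The follow-up text does explain why staff cannot match a record to a person, but it attaches that explanation to the individualized link and gives no counterpart for the phone. These statements cannot all hold for a phone-completed survey.

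**2. What the assistant learns.** The code questions open each survey, and the protocol does not say they are handled differently by phone. Unless they are, the assistant hears both the code answers and the perpetration answers of a known youth. The stored record still carries only a self-made code and no name.

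**3. Who calls.** The text says only that it is a research assistant. Section 8.2 gives each neighborhood a designated point assistant but does not assign that person the survey calls. Prior contact with the youth is therefore possible, not stated.

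**4. The plan's own figure, as a yardstick.** Section 9.2 gives 80% power for an 8.3-point fall from 20% (to 11.7%), with 866 youth, 21 clusters, ICC 0.01, 80% retention and a two-sided 5% test.
- Analyzed: 866 × 0.8 = 692.8, or 692.8 / 21 = 33 per cluster.
- Design effect: 1 + (33 − 1) × 0.01 = 1.32. Effective N: 692.8 / 1.32 = about 525, split 10:11.
- Power from a pooled two-proportion test: 74.3%, not 80%.

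That shortfall is a separate matter. Here 74.3% serves only as the reference for step 6.

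**5. Unequal under-reporting, no true effect.** Let f be the share of T3 surveys done by phone, and u the share of would-be disclosers who deny by phone. Both are assumptions. The reported rate is the true rate × (1 − f × u). With a 20% true rate in both arms, the spurious difference is 0.20 × f × (u in intervention − u in control).
- Lower end: 0.20 × 0.10 × 0.25 = 0.5 points, or 0.5 / 8.3 = 6% of the design effect.
- Upper end: 0.20 × 0.30 × 0.50 = 3.0 points, or 3.0 / 8.3 = 36%.
- At f = 5% the range is 0.25 to 0.5 points.
- With a gap of zero it is 0. With a gap of the opposite sign, the same sizes count against the intervention.

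**6. Equal under-reporting, true effect of 8.3 points.** The observed difference is 8.3 × (1 − f × u). At f = 20%: 8.3 × 0.95 = 7.9 and 8.3 × 0.90 = 7.5.

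| Phone share f | Spurious benefit, denial in intervention arm only, u = 25% to 50% | Chance of false benefit (2.5% if unbiased) | Observed difference if denial is equal, u = 25% to 50% | Power (74.3% if unbiased) |
|---|---|---|---|---|
| 10% | 0.5 to 1.0 | 3.5% to 4.8% | 8.1 to 7.9 | 73.0% to 71.7% |
| 20% | 1.0 to 2.0 | 4.8% to 8.5% | 7.9 to 7.5 | 71.7% to 69.0% |
| 30% | 1.5 to 3.0 | 6.4% to 14.2% | 7.7 to 7.1 | 70.3% to 66.1% |

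Differences are in percentage points.

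**The case against.** The phone is one option among several. Section 8.1 puts tablet completion first and the link next for those who cannot attend, so the phone share may be close to zero. Participants know their program in every mode, so any tendency to give the approved answer exists on the tablet too; the phone can only add to it. The direction is open as well: a program that teaches boys to identify coercive behavior could raise reporting rather than lower it. Remote completion also supports the 80% T3 retention that Section 9.2 assumes, so banning spoken perpetration items could lose data from youth without a device, possibly a selective group.

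All of this stands. It limits the size of the concern and rules out an outright ban as the remedy. It does not remove the contradiction between the passages.

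A reader might infer that the bias favors the intervention. No passage shows denial differing by arm. A reader might also infer a broken promise of confidentiality. The documents do not show one: assistants belong to the research team that holds the data in confidence, no name is stored with the survey, and a Certificate of Confidentiality applies. Nor is it a finding that the protocol lacks an analysis by completion mode, since that may sit in a statistical analysis plan not seen here.

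**Conclusion.** The point holds in limited form. The phone option in Section 8.1 contradicts the statements in Sections 4.1, 8.1 and 10.1.9.1 that surveys are anonymous, self-entered, and completed on a tablet or through a link. For youth who choose the phone, anonymity towards an unblinded assistant is lost at the primary time point, which opens an avoidable route to under-reporting. It would be wrong to say that the primary outcome as a whole loses its anonymity, because tablet and link completion are unaffected.

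The size is unknown. The 0.5 to 3.0 point range rests wholly on an assumed phone share and an assumed gap in denial between arms, and its top needs both at their extremes. With equal denial there is no spurious effect under the null, only dilution of a true one. The contradiction itself rests on no assumption.

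**What to change.** 1. In Section 8.1, Follow up surveys, offer self-entry by texted or emailed link first and keep the phone interview as a fallback for youth who cannot use it.
2. Have phone interviews done by an existing assistant from another neighborhood who did not attend that youth's sessions and is not told the arm. This masks the caller only; the youth still knows which program he had.
3. Store the mode of completion with each survey record, so that mode can be reported by arm and the primary analysis repeated without phone-completed T3 surveys.
4. Reconcile Sections 4.1, 8.1 (Data Collection, Data Management, Outcomes) and 10.1.9.1 with the phone option, so that phone surveys are called confidential rather than anonymous or self-entered.

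The cost is protocol wording, one database field and a reallocation of calls among existing assistants. The downside is some loss of familiarity between caller and youth. Keeping the phone as a fallback avoids giving up T3 data.
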